### Randomisation

Randomisation will occur once all 30 participants have been recruited and baseline measures have been completed. In order to obtain sufficient data on the intervention, we will utilise simple block randomisation with unbalanced allocation so that 20 participants receive the intervention and 10 are allocated to the wait-list control group. A researcher independent of the study team will perform the randomisation using the Experimental Design Generator and Randomiser (EDGAR-II) [65] and inform the music therapists and unblinded member of the study team of the allocation by email. The music therapists will then inform participants of their allocation and provide additional support if required.

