### Outcome measures and endpoints

Our primary interest is in the feasibility of the trial design and intervention. A summary of the main feasibility outcomes, success criteria and timing is shown in Table 1. Proposed clinical outcomes are:

**Table 1 Tab1:** Methods and timing for assessing, recording and analysing outcome parameters

Outcome	Method	Success criteria				Timing
		Stop	Continue, modify protocol	Continue without modification but monitor closely	Continue without modifications	
Acceptability of methodology	Recruitment and retention rates as below					End of recruitment (week 8)
	Compliance	Mean attendance <10 sessions	Mean attendance <14 sessions	Mean attendance 14 sessions	Mean attendance 14+ sessions	End of intervention (week 22)
	End interviews	Unfavourable views, serious concerns	Unfavourable views, suggestions for modification	Favourable views, suggestions for modification	Favourable views, no concerns	1 month post-intervention (week 26)
Feasibility of recruitment processes	Screening rates	Identify <50 potentially eligible subjects	Identify <100 potentially eligible subjects	Identify 100–128 potentially eligible subjects	Identify >128 potentially eligible subjects	End of recruitment
	Recruitment rates	Recruit <50% of sample size	N <25 in 8wks, <5% per week	*N* = 25–30 in 8wks, <13% per week	*N* = 30 in 8wks, 13% per week or greater	End of recruitment
	Participation rates	Participation rate <5%	Participation rate 5–15%	Participation rate 15–25%	Participation rate 25% or greater	6 months post-intervention
	Retention rates	Attrition >75%	Attrition 50–75%	Attrition 30 − 50%	Attrition <30%	6 months post-intervention
	End interviews	N/A	Major suggestions to improve recruitment processes	Minor suggestions to improve recruitment processes	No suggestions to improve expressed	1 month post-intervention (week 26)
Identify number of eligible participants, participant rates and retention rates	Number identified by HCPs	<50 identified	50–100 identified	100–128 identified	>128 potentially eligible identified	End of recruitment
	Number expressing interest	<30 express interest	30–40 express interest	40–60 express interest	>60 express interest	End of recruitment
	Number providing consent	<15 provide consent	15–25 provide consent	25–30 provide consent	30 provide consent	End of recruitment post-intervention, 3 and 6 months post-intervention
	Number lost to follow up	Attrition >75%	Attrition 50–75%	Attrition 30–50%	Attrition <30%	

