Researcher time and costs per participant	Researcher diary	N/A	Researcher time exceeds allocated time requiring additional study support	Researcher time and cost only just covers time required	Researcher time and cost fully covers time required	6 months post-intervention
Appropriate outcome measures	Variability of outcome Estimate of control mean and SD of change	No difference or clinically important difference favouring control detected based on confidence limits	Difference cannot be detected based on confidence limits but data suggest improvement favouring intervention	Difference can be detected based on confidence limits	Clinically important difference can be detected based on confidence limits	End of intervention
Intervention components	Therapist adherence	Adherence <50%	Adherence <50%	Adherence 50–75%	Adherence >75%	End of intervention
	End interviews	Serious concerns expressed regarding intervention	Major suggestions to adapt intervention	Minor suggestions to adapt intervention	No concerns or suggestions to adapt intervention	
Intervention adherence	Therapist self-rated adherence Video-rated adherence	Adherence <25%	Adherence 25–50%	Adherence 50–75%	Adherence >75%	End of intervention
Estimate of cost of intervention and services received	Therapist time CSRI	Cost significantly greater than usual care, no potential to modify intervention, no indication of benefits	Cost is greater than usual care - intervention may be modified, but outcomes suggest some benefits	Cost is greater than usual care but outcomes strongly suggest benefits	Cost is equivalent to or slightly greater than usual care, outcomes strongly suggest benefits	6 months post-intervention

*HCPs* healthcare professionals, *N/A* not applicable, *CSRI* Client Services Receipt Inventory

Observer rated:Symptoms of depression as measured by the Montgomery-Åsberg Depression Rating Scale (MADRS) [62, 66, 67]Social functioning as measured by the life skills profile (LSP) [68]Level of hospitalisation as measured by admission, length of stay and number of readmissions

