### Sample size

This study aims to assess the feasibility of recruitment processes including the number of eligible participants and participation/retention rates. Papers considering sample size for feasibility and pilot studies suggest the inclusion of upwards of 24–50 participants [59, 90, 91]. The present study aims to recruit 30 patients to participate in three groups of 10 patients each. In order to obtain sufficient data on the intervention, randomisation will be imbalanced so that 20 are randomised to the treatment arm and 10 to the wait-list control group.

Studies of wider psychosocial and psychotherapeutic interventions for chronic depression show participation rates in the range of 25–33% of eligible patients consenting to participate in the study [92–94]. With a sample size of 30, we will be able to estimate a participation rate of 25% to within a 95% confidence interval of +/-15%. Assuming that one fifth of patients accessing primary care for depression will have developed chronic depression, we estimate approximately 1300 patients within primary care will be eligible for this study. We estimate each practice will have around 100 patients with depression, of which around 20 will have enduring symptoms. Within the secondary care sites in which we plan to recruit, there are currently around 1960 patients with a diagnosis of depression. Assuming that one fifth will have developed chronic depression [1], we estimate approximately 392 patients within secondary care will be eligible for this study. Based on a participation rate of 25%, we plan to approach 128 patients with the aim of recruiting 4 per week, over 8 weeks.

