### Statistical analysis

#### Feasibility

As this is a feasibility study, the main statistical reporting will comprise descriptive statistics and calculation of effect sizes. We will assess:• Acceptability of methodology to professionals and patients through interviews via recruitment rates, compliance, end interviews      • Feasibility of recruitment processes• Deviation around specific post-intervention, and 3-month and 6 month post-intervention follow-up assessment dates for actual data collection• Number of eligible participants, participation rates and retention rates• Researcher time and costs per participant• Appropriateness of outcome measures

Descriptive analyses will establish recruitment and drop-out rates and the distribution of baseline characteristics and all outcomes post-intervention, and 3 months and 6 months post-intervention. The research team will reflect upon the representativeness of the demographics in terms of the general population of patients that could potentially be useful in assessing the intervention.

Recruitment and drop-out rates will be monitored on a monthly basis allowing for examination and reporting of patterns and whether there are any obvious trends. This may inform the choice of the primary outcome for a full-scale trial allowing for drop-outs in a sample-size calculation.

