#### Clinical outcomes

This study will employ intention-to-treat analysis. Data from all subjects will be included in the analysis as randomised. Adverse events will be reported by sub-groups of those who were currently receiving the intervention and those who were not.

We will first calculate a mean value of the outcome for each unit and present them with confidence intervals. Outcomes will be compared between intervention and control groups using linear regression models, adjusting for the baseline score of the given outcome. The confidence limits of each treatment effect and knowledge of the clinically important difference (where this is available) will be used to determine whether clinically important differences are ruled out by these confidence limits. The intra-cluster correlation coefficient will be calculated. Due to the small sample size, this estimate is likely to be imprecise, therefore we will also use estimates in the literature from similar studies for comparison to inform the design of any future studies. We will descriptively explore in sub-group analyses whether there are any differences between compliant and non-compliant attenders, responders and non-responders and whether any socio-demographic and clinical characteristics are associated with outcomes. As a preliminary economic evaluation, we will calculate the cost of delivery of music therapy and cost of services received by both groups using the CSRI [83]. This will be descriptive only to provide an estimate for future studies.

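### The one stated model, baseline-adjusted linear regression, does not suit the hospitalisation outcome, and with no events its interval collapses to 0 to 0 (minor)

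*Protocol article*

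**What the plan says.** Under Outcome measures and endpoints, the article introduces a list with "Proposed clinical outcomes are". Its third observer-rated item, after the MADRS and the Life Skills Profile, is "Level of hospitalisation as measured by admission, length of stay and number of readmissions".

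Under Statistical analysis, Clinical outcomes, the between-arm comparison is given in one sentence: "Outcomes will be compared between intervention and control groups using linear regression models, adjusting for the baseline score of the given outcome". The next sentence says that the confidence limits of each treatment effect and "knowledge of the clinically important difference (where this is available) will be used to determine" whether such differences are excluded. No second model is named for binary, count or zero-heavy outcomes. The only item in that section set apart as descriptive only is the preliminary economic evaluation based on the CSRI.

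Under Randomisation, "20 participants receive the intervention and 10 are allocated to the wait-list control group". Under Feasibility, "the main statistical reporting will comprise descriptive statistics and calculation of effect sizes".

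**The concern.** Admission is yes/no. Length of stay is zero for everyone not admitted and has a long tail among the rest. The number of readmissions is a rare count. None of these has a baseline score in the sense that a rating scale has one. If no one was admitted before entry, the baseline covariate is constant and the stated adjustment cannot be made.

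A linear model fitted to such data in 30 patients takes its standard error from a handful of non-zero values. In the extreme case of no events in either arm, the residual variance is zero and so is the width of the interval. The output then looks like precise evidence of no difference when the data say very little. Hospitalisation figures are also likely to be carried into planning the full trial, so an interval that misstates their uncertainty could mislead there.

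**Working it through.** **The plan's own precision figure.** The only one is for participation: "estimate a participation rate of 25% to within a 95% confidence interval of +/-15" per cent with n = 30. Check: 1.96 × √(0.25 × 0.75 / 30) = 0.155, which agrees within about half a point. It has no bearing on hospitalisation, for which no precision is stated.

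**Inputs from the article.** 20 intervention and 10 wait-list patients; linear regression adjusted for baseline. The 95% level is stated only for the participation rate and is assumed here for treatment effects.

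**Assumptions, not in the article.** Admission rate p per assessment window of 2% to 30%; a quarter of admitted patients readmitted; mean stay of 20 days if admitted.

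**1. No events in either arm.** Every outcome value is 0, so the estimate is 0, the residual sum of squares is 0 and the interval is [0, 0]. What the same data support:
- Exact (Clopper-Pearson) upper limits: 1 − 0.025^(1/20) = 16.8% for 0/20 and 1 − 0.025^(1/10) = 30.8% for 0/10.
- Newcombe interval for the risk difference, intervention minus control: −27.8 to +16.1 percentage points.

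**2. How often the interval collapses.**

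| Assumed admission rate p | No admission in 30: (1 − p)^30 | No admission in 21 (30% attrition): (1 − p)^21 | No readmission in 30: (1 − 0.25p)^30 |
|---|---|---|---|
| 2% | 55% | 65% | 86% |
| 5% | 21% | 34% | 69% |
| 10% | 4% | 11% | 47% |

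No admissions among the 10 controls alone does not collapse the interval. One 20-day admission in the intervention arm gives a difference of 1 day. The residual sum of squares is 400 − 20 = 380, the residual variance 380/28 = 13.57 and the standard error √(13.57 × (1/20 + 1/10)) = 1.43. With t = 2.048 on 28 df, the interval is −1.9 to 3.9 days before baseline adjustment.

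**3. Coverage of the nominal 95% interval for length of stay.** Simulation of 40,000 trials, 20 versus 10, stay = Bernoulli(p) × lognormal (mean 20 days, log-SD 1), unadjusted pooled-variance interval. Zero-width intervals count as misses when the arms truly differ.
- 10% control versus 5% intervention: 76%.
- 15% versus 5%: 74% to 75%.
- 5% versus 10%: 83%.

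With the baseline covariate included and a gamma stay (mean 20 days, CV 1; 20,000 runs), 10% versus 5% again gives 75%. Over a wider set of unequal rates, coverage runs from 51% (5% versus 2%) to 87% (20% versus 10%). Leaving out zero-width intervals, it is still 78% to 88%, so collapse is not the whole cause.

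For yes/no admission, collapse explains most of the loss at low rates. At 10% versus 5%, coverage is 84% overall and 96% among the other runs.

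**4. Equal rates in both arms (2% to 20%).** Coverage for length of stay is about 97% to over 99%, and for admission 96% to 99%. The interval is then conservative.

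**The case against.** The strongest defence is that the sentence was written for rating scales. Most of the listed outcomes are scales, the phrase about a baseline score fits only those, and the choice of model by outcome type is often left to an analysis plan or full protocol that is not shown here. The authors may well have had scales in mind. But the text does not limit the model to them, hospitalisation is in the same list, and the authors did mark an exception for the economic evaluation. This is a stated method that fits one listed outcome badly, not silence.

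Three stronger readings are tempting and are not supported:
- **That the plan would falsely rule out a difference in hospitalisation.** That step operates only where a clinically important difference is available, and the article gives none for hospitalisation. The risk arises only if one were adopted.
- **That the limits are badly wrong in general.** With equal rates they are conservative. The failure depends on very few events or on a true difference, and the article gives no admission rate. Recruitment includes secondary-care teams, so rarity of admission is itself an assumption.
- **That a collapsed interval could trigger the Stop band in Table 1.** The row on appropriate outcome measures refers to confidence limits but does not say which outcome it applies to, and no row names hospitalisation.

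It is also fair to say that the main reporting is descriptive, so a reader would see 0/20 and 0/10 beside the interval. That limits the harm but does not make the interval meaningful.

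**Conclusion.** The point holds in a limited form. The stated linear regression is unsuited to admission, length of stay and readmissions with 20 versus 10 patients. Its interval has zero width if there are no events, and it under-covers length of stay when the arms truly differ. Collapse is plausible for admission and stay at assumed rates of 2% to 5% and unlikely at 10% with all 30 analysed. For readmissions it remains close to even odds at 10%, given the further assumption that a quarter of those admitted are readmitted. All rates and stay distributions are assumptions, because the article gives none.

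The severity is minor. This is one of 11 proposed clinical outcomes in a mainly descriptive feasibility trial, and the MADRS, the proposed primary clinical outcome, and the other rating scales are not touched.

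**What to change.** In the Clinical outcomes section, restrict the baseline-adjusted linear regression to the rating-scale outcomes and add one sentence for hospitalisation. By randomised arm, report:
- number admitted over number randomised, with exact or score-based 95% limits;
- bed-days, with patients never admitted counted as zero;
- readmissions as a plain count.

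State that no conclusion about a difference being ruled out will be drawn from this outcome.

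The change needs no new data. Its cost is that hospitalisation gets no model-based effect estimate, which 30 patients could not support in any case.

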### Estimation and appropriateness of outcomes

We expect to see changes in a range of clinical and social outcomes. However, we do not yet know which measures might be most appropriate in terms of acceptability of completion and variability of outcome. Our proposed primary outcome is symptoms of depression, measured by an observer-rated scale (Montgomery-Åsberg depression rating scale [62]). We will also measure potential changes in self-rated depression, social functioning, psychological distress, self-esteem, self-efficacy, mood, relationships, satisfaction with treatment, work and social adjustment, quality of life and service use. We will examine the acceptability and provide descriptive statistics and estimates of effect of the proposed outcome measures to inform the design of a future randomised controlled trial. As we are providing a group intervention, we also plan to estimate the intra-cluster correlation coefficient to take this into account in conjunction with future sample size calculations. To aid estimation of the cost of the intervention, we plan to conduct a preliminary economic analysis to estimate the cost of services received by the intervention and control groups.

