### Wait-list control

The wait-list control group will receive treatment as usual whilst study measures are completed and will then be eligible to receive group music therapy once the 6-month follow up has been completed. Receipt of services will be assessed throughout this time in both arms to enable an initial description of the types of services received and associated cost.

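### The confidence limits for the treatment effect make no allowance for clustering in the two therapy groups, so they are too narrow if the residual ICC is above zero, and two groups give almost no information on that ICC

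*Protocol article*

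**What the plan says.** All references are to the protocol article.

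- **Model** (Clinical outcomes): "Outcomes will be compared between intervention and control groups using linear regression models, adjusting for the baseline score of the given outcome". Baseline score is the only adjustment named. The section then uses the confidence limits, with the clinically important difference where one is known, to decide whether such a difference is excluded. In Table 1, the row on appropriate outcome measures grades the trial from stop to continue according to what the limits show.
- **Group structure** (Sample size): "The present study aims to recruit 30 patients to participate in three groups of 10 patients each", and "randomisation will be imbalanced so that 20 are randomised to the treatment arm and 10 to the wait-list control group".
- **Controls** (Wait-list control): they "will then be eligible to receive group music therapy once the 6-month follow up has been completed".
- **ICC** (Estimation and appropriateness of outcomes): "we also plan to estimate the intra-cluster correlation coefficient to take this into account in conjunction with future sample size calculations". Clinical outcomes repeats that "The intra-cluster correlation coefficient will be calculated", says the estimate will probably be imprecise because the sample is small, and adds that literature estimates will be consulted for comparison when future studies are designed.

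**The concern.** Patients treated in the same group share therapists, sessions and each other. The protocol's own rationale relies on shared experience, bonding and stable membership, so outcomes within a group may well be correlated. The protocol recognises this for future trials, yet nothing in the stated analysis applies an ICC, its own or a published one, to this trial's limits.

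At stake is the calibration of those limits. They serve two stated purposes: judging whether a clinically important difference is excluded, and placing the result in a Table 1 grade. Limits that are too narrow make both judgements look firmer than they are.

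A second, smaller matter is the reason given for the ICC's imprecision. The text attributes it to the number of patients. The binding constraint is the number of groups.

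**Working it through.** **Plan's own figure.** There is none on this point: no ICC, design effect or interval width for a treatment effect is stated. The only precision figure, ±15% around a 25% participation rate with n = 30, reproduces as 1.96 × √(0.25 × 0.75 / 30) = 0.155, but does not bear on clustering.

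**Structure.** Thirty patients in groups of 10, with 20 in the intervention arm, gives two treated groups. The third group starts after the 6-month visit, so it adds no treated cluster to the outcome data. The data are therefore 2 × 10 clustered patients against 10 unclustered ones. Two groups is an inference, but the only one these figures support.

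**Standard error.** Take an outcome variance of 1, group size m = 10 and an ICC of ρ.

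- Under independence: Var = 1/20 + 1/10 = 0.15
- With clustering in the treated arm only: Var = (1 + 9ρ)/20 + 1/10
- SE ratio = √{[(1 + 9ρ)/20 + 1/10] / 0.15} = √(1 + 3ρ)
- Actual error of a nominal 5% test (normal approximation) = 2 × [1 − Φ(1.96 / ratio)]

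The values of ρ are assumptions.

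| ρ | Treated-arm design effect, 1 + 9ρ | SE ratio | Actual error | Simulated coverage of the ordinary 95% interval |
|---|---|---|---|---|
| 0.01 | 1.09 | 1.015 | 5.3% | 94.4% |
| 0.05 | 1.45 | 1.072 | 6.8% | 93.0% |
| 0.10 | 1.90 | 1.140 | 8.6% | 91.3% |
| 0.20 | 2.80 | 1.265 | 12.1% | 86.8% |

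The last column comes from 40,000 simulated trials per value, using a two-sample comparison on 28 df without baseline adjustment or dropout.

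**Effect of attrition.** With 2:1 allocation kept, the ratio is √(1 + (m − 1)ρ/3). At 30% loss in both arms, m = 7 and the ratio is √(1 + 2ρ): 1.049 at 0.05, 1.095 at 0.10 and 1.183 at 0.20.

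**Precision of the ICC.** A one-way analysis of two groups of 10 has 1 and 18 df. For an observed ICC of 0.05:

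- F = (1 + 9 × 0.05)/(1 − 0.05) = 1.526
- Lower limit: with F_L = 1.526 / F₀.₉₇₅(1, 18), (F_L − 1)/(F_L + 9) = −0.08
- Upper limit: with F_U = 1.526 × F₀.₉₇₅(18, 1), (F_U − 1)/(F_U + 9) = 0.99

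In the same simulation, at a true ICC of 0.05 the estimate is negative in 57% of trials and its central 95% range is −0.11 to 0.45. At a true ICC of 0.10 it is negative in 50%. Adding patients to each group leaves the between-group df at 2 − 1 = 1.

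**What a cluster-aware interval would cost.** In SD units, at ICC 0.05 the median half-width is 0.78 for the ordinary interval and 0.92 for one based on the two group means with Satterthwaite df. If the ICC were known it would be 1.96 × √(1.45/20 + 0.10) = 0.81. At ICC 0.10 the three figures are 0.77, 0.97 and 0.87.

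**The case against.** **The article is condensed.** It names no variance estimator, and a fuller document might add one. The sentence "We will first calculate a mean value of the outcome for each unit and present them with confidence intervals" might mean summaries by therapy group. These points are fair, but *unit* is undefined, the regression sentence carries no group summary forward, and the article does state the model, its adjustment and the decision use of its limits.

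**The size depends on an ICC that nobody has stated.** This stands. At 0.01 the error is negligible. Attrition reduces it, and after baseline adjustment only the residual ICC counts. The claim must therefore be conditional.

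**The decision impact is limited.** This largely stands too. Three of the four grades in the Table 1 row mean continuing, the row is one of many, and the main reporting is descriptive. Limits that are somewhat too narrow would mostly move a result between continue grades. No stop decision has been shown to change.

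**The ICC imprecision is already disclosed.** It is, and this rules out two stronger readings that a reader might infer:

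- That the ICC objective cannot be met. The objectives set no precision target, and an ICC can be calculated from two groups.
- That the trial's own ICC will make the next trial too small. That assumes it is used alone, whereas the protocol plans literature values alongside it. With a range of −0.11 to 0.45, it could also err towards too large a trial.

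What remains is the misattributed cause and the little weight the estimate deserves.

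**Conclusion.** The concern holds in conditional form. The stated regression has no allowance for therapy group, and its limits are interpreted. If the residual ICC is above zero they are too narrow: trivially at 0.01, and materially from about 0.05 upwards (SE 7% too small at 0.05, 14% at 0.10 and 26% at 0.20, each expressed as the excess of the true SE over the reported one). These figures assume two full groups of 10, unclustered controls, equal variances and an assumed ICC. They shrink with smaller groups.

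The documents do not support saying that the limits are too narrow whatever the ICC. On the ICC itself, the sound conclusion is that it can be reported but carries almost no information, because there are two groups. For a feasibility trial with mainly descriptive reporting, this is worth correcting but does not undermine the design.

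**What to change.** 1. In Clinical outcomes, state that each treatment effect is also reported with the intervention-arm variance multiplied by 1 + (m − 1) × ICC. Here m is the group size actually analysed, and the ICC runs over a range from the literature the team already plans to consult, for example 0.01 to 0.10.
2. Use these wider limits wherever Clinical outcomes or Table 1 interprets confidence limits.
3. Say plainly that the inflation relies on an assumed ICC and does not remove the limit of one between-group degree of freedom. The gap between the half-widths of 0.81 and 0.92 SD at ICC 0.05 shows what is left uncovered.
4. Report the trial's own ICC with its interval, attribute its imprecision to the number of groups, and base the future design effect on the literature values.
5. Define *unit* in the sentence on mean values.

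The cost is a few lines of analysis text and slightly wider intervals. No further patients or data are needed.
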